## Abstract

**Introduction:**

The time during which many attend college or university is an important period for developing health behaviours, with potentially major implications for future health. Therefore, it is concerning that many Swedish students excessively consume alcohol, have unhealthy diets, are not physical active and smoke. The potential of digital interventions which integrate support for change of all of these behaviours is largely unexplored, as are the dismantled effects of the individual components that make up digital lifestyle behaviour interventions.

**Methods and analysis:**

A factorial randomised trial (six factors with two levels each) will be employed to estimate the effects of the components of a novel mHealth multiple lifestyle intervention on alcohol consumption, diet, physical activity and smoking among Swedish college and university students. A Bayesian group sequential design will be employed to periodically make decisions to continue or stop recruitment, with simulations suggesting that between 1500 and 2500 participants will be required. Multilevel regression models will be used to analyse behavioural outcomes collected at 2 and 4 months postrandomisation.

**Ethics and dissemination:**

The study was approved by the Swedish Ethical Review Authority on 2020-12-15 (Dnr 2020-05496). The main concern is the opportunity cost if the intervention is found to only have small effects. However, considering the lack of a generally available evidence-based multiple lifestyle behaviour support to university and college students, this risk was deemed acceptable given the potential benefits from the study.

Recruitment will begin in March 2021, and it is expected that recruitment will last no more than 24 months. A final data set will, therefore, be available in July 2023, and findings will be reported no later than December 2023.

**Trial registration number:**

ISRCTN23310640; Pre-results.

Strengths and limitations of this studyA factorial trial is used to estimate the effects of the components of a novel mHealth intervention on four important health-related behaviours: alcohol consumption, diet, physical activity and smoking.Employing a Bayesian group sequential design will ensure that the trial will not be underpowered, nor recruit more participants than necessary.Self-reported outcomes are used, which may be vulnerable to bias from research participation effects, including the risk of detection bias from telephone follow-ups.Mediators are measured using single face-valid items rather than validated questionnaires in order to reduce participant burden.

## Introduction

Non-communicable diseases (NCDs), such as cardiovascular diseases and cancers, constitute a major public health concern by causing 71% of deaths globally each year.^1^ The WHO has made it clear that the burden of disease that NCDs cause would be greatly reduced if the prevalence of harmful alcohol consumption, unhealthy diets, physical inactivity and smoking^2^ was reduced. Behavioural risk factors, such as an individual’s lifestyle, additionally accounted for 36% of all disability-adjusted life years in 2017 globally.^3^ Thus, it is important to find effective and scalable means of helping individuals to improve their lifestyle behaviours in order to improve health and well-being.

Many health-related behaviours are established during adolescence and young adulthood and frequently persist into adulthood.^4–6^ The time during which many attend college or university is an important period for developing healthy lifestyle behaviours, with potentially major implications for future health. Becoming a student is in Sweden often associated with several new commitments, such as caring for a household, building new social networks and dealing with basic household economics. It is, therefore, particularly concerning that many Swedish students have unhealthy lifestyle behaviours.^7 8^

While there is a lack of specific data regarding college and university students’ lifestyle behaviours in Sweden, data on the 18–29 age group from the Public Health Agency of Sweden’s national public health survey from 2018 (n=1925) suggest that the majority of these individuals (94%) report at least one risk behaviour: 17% were smokers (5.4% daily and 11.1% occasionally), 25% had a risky alcohol consumption, 28% were not sufficiently physically active, 92% did not eat enough fruit and vegetables and 32% were overweight or obese. Approximately 27% reported two or more risk behaviours, risky drinking and not eating enough fruit and vegetables being the most common. Consequently, it is important to empower young adults with the knowledge, attitudes and life skills necessary for making informed decisions that are protective of good health and can reduce the future risk of NCDs.^9^

### Digital interventions and mHealth

Young adults are digital natives having easy access to technology and commonly use apps and the internet to seek health information.^10^ Therefore, using digital devices represents a well-established means of delivery of personalised health interventions to young adults.^10–12^ Interventions which use mobile technologies, often referred to as *mHealth* interventions, are of particular interest as they offer new potential in delivering behaviour change support in individuals’ everyday life.

Several *single* behaviour digital lifestyle interventions have been evaluated among college and university students over the past decades,^13–16^ including various combinations of delivery modes, such as text messaging and web-based platforms.^17–24^ In Sweden for instance, research on digital interventions have shown promising results with respect to alcohol,^25–32^ smoking cessation^33 34^ and mental health promotion.^35^ However, few studies investigate interventions which aim to change two or more unhealthy lifestyles simultaneously.^36–41^ Thus, while the potential of digital behaviour interventions is promising, knowledge about the effects of digital *multiple* lifestyle interventions is limited—despite unhealthy behaviours tendency to co-occur.^42^

In addition to the evidence for digital multiple lifestyle interventions being limited, current evidence for behaviour interventions lacks detail with respect to the effects of the components of interventions. While there have been trials which aim to dismantle the effects of intervention components,^25 43 44^ most trials estimate the effects of interventions as a whole.^45^ Increasing our understanding of the effects at the component level, in particular with respect to multiple lifestyle behaviours, may help move the field of behaviour interventions forward.

### Aims and objectives

The aim of this study is to estimate the effects of the components of a novel mHealth intervention on multiple lifestyle behaviours (alcohol, diet, physical activity and smoking) among college and university students in Sweden. The study is a part of the Mobile health Multiple Behaviour Interventions across the LifEspan research programme (MoBILE),^46^ which contains seven projects on multiple lifestyle interventions among different populations across the lifespan. The objectives of the study are to:

Estimate the effects of a novel mHealth intervention’s different components on individual lifestyle behaviours:Weekly alcohol consumption and number of episodes per month of heavy drinking.Weekly consumption of sugary drinks and average daily fruit and vegetable consumption.Weekly moderate to vigorous physical activity (MVPA).Four-week point prevalence of smoking.Estimate the degree to which the effects of the components are mediated through perceived importance, confidence and know-how.Detect interactions among lifestyle behaviour change, for example, those who stop smoking may also reduce their alcohol consumption, and the degree to which this is moderated by the components of the intervention.

## Methods

A factorial randomised trial^47^ (six factors with two levels each) will be employed to address the objectives of the study. A Bayesian group sequential design will be employed to periodically make decisions to continue or stop recruitment.^48–50^ This protocol contains relevant items from the *Standard Protocol Items: Recommendations for Interventional Trials*.^51^

### Study setting, recruitment and eligibility

All 31 college and universities in Sweden will be invited to participate in the trial, and we anticipate that the majority will accept. Participating universities will recruit students to the trial using: (1) paper advertising (posters and leaflets), (2) digital advertising (email, website, social media) and (3) through student healthcare staff. Students will register their interest by sending a text message to a dedicated telephone number (included in all information materials). In response, students will receive a text message with a hyperlink to a web page presenting informed consent materials (online supplemental appendix A). All students who consent, by clicking on a button after reading the informed consent materials, will immediately be asked to complete an online baseline questionnaire (online supplemental appendix B), which will also be used to assess eligibility for the trial.

10.1136/bmjopen-2021-051044.supp1Supplementary data

10.1136/bmjopen-2021-051044.supp2Supplementary data

Students will be included in the trial if they fulfil at least one of six conditions:

**Weekly alcohol consumption:** consumed 10/15 (female/male) or more standard drinks of alcohol the past week. A standard drink of alcohol is in Sweden defined as 12 g of pure alcohol.
**Heavy episodic drinking:** consumed 4/5 (female/male) or more standard drinks of alcohol on a single occasion at least once the past month.
**Fruit and vegetables:** consumed less than 500 g of fruit and vegetables on average per day the past week.
**Sugary drinks:** consumed 3 or more units of sugary drinks the past week. One sugary drink unit is defined as approximately 33 cl.
**MVPA:** spent less than 150 min on MVPA the past week.
**Smoking:** having smoked at least one cigarette the past week.

Students will be explicitly excluded if they do not fulfil any of the criteria or if they are less than 18 years of age. The trial information and intervention will be entirely in Swedish and delivered to participants’ mobile phones, thus not comprehending Swedish well enough to sign up or not having access to a mobile phone will implicitly exclude participants.

### Interventions

The *Buddy* multiple lifestyle behaviour intervention is an mHealth intervention which consists of six components which users access using their mobile phone, based on an intervention design we have used previously.^52^ The intervention is designed around social cognitive theories of behaviour change, with a focus on modifying environment, intention, and skills.^53 54^ Please see online supplemental appendix C for full details. The intervention’s components are intended to be used as a toolbox, allowing users to choose which parts of the intervention to interact with and tailor the support to their needs. The intervention materials can be accessed at participants’ discretion over a 4-month period, and each Sunday afternoon participants will receive a text message with a link and a reminder to access *Buddy*.

10.1136/bmjopen-2021-051044.supp3Supplementary data

The six components of the intervention are: (1) screening and feedback, (2) goalsetting and planning, (3) motivation, (4) skills and know-how, (5) mindfulness, and (6) self-authored text messages. These components will also represent factors in the factorial trial. Participants eligible for the trial will be randomly allocated to 1 of 64 factorial conditions, each condition representing a unique combination of *Buddy*’s six components—which are either present or absent (2^6^=64 conditions). They will remain in the same condition for the entirety of the 4-month intervention period. For a more detailed description of each component, including a full specification of each factorial condition, please see online supplemental appendix C.

### Outcomes

#### Measures

Outcomes are listed here and subsequently explained. All questionnaires (baseline, 1-month, 2-month and 4 month follow-up) used in the trial are found in online supplemental appendix B.

##### Primary outcome measures

**Alcohol:** weekly alcohol consumption; monthly frequency of heavy episodic drinking.
**Diet:** average daily consumption of fruit and vegetables; weekly consumption of sugary drinks.
**Physical activity:** weekly MVPA.
**Smoking:** 4-week point prevalence of smoking abstinence.

##### Secondary outcome measures

Weekly consumption of candy and snacks.Body mass index (BMI).Number of cigarettes smoked the past week.Perceived stress.

##### Mediation measures

Importance of change.Confidence in one’s ability to change.Knowledge of how to change.

#### Primary and secondary outcome measures

Weekly alcohol consumption will be assessed by asking participants the number of standard drinks of alcohol they consumed last week (short-term recall method^55^). Frequency of heavy episodic drinking will be assessed by asking participants how many times they have consumed more than 4/5 (female/male) standard drinks of alcohol on one occasion the past month. These two outcomes are both part of the proposed core outcome set for brief alcohol interventions.^56–58^

Diet and physical activity will be measured using a questionnaire based on the previously published questionnaire by the National Board of Health and Welfare in Sweden^59^ and was further modified to also include portion sizes. The consumption of fruit and vegetables will be measured using two questions concerning the number of portions (100 g) of fruit and vegetables (respectively) the participants ate on average per day during the past week. Sugary drink consumption will be measured by a question regarding the number of units (33 cl) of sugary drink participants consumed the past week. MVPA will be estimated by summing responses to two questions regarding the number of minutes spent on moderate and vigorous physical activity, respectively, during the past week.

BMI will be measured by asking participants to report their weight (both weight and height have been reported at baseline, and height is unlikely to have changed significantly and will, thus, only be asked at baseline).

Four-week point prevalence of smoking abstinence (no cigarettes the past week) will be asked as a binary question. This is a suggested measure by the Society of Research on Nicotine and Tobacco.^60^ Participants who have smoked any cigarette the past 4 weeks will be asked for the number of cigarettes smoked the past week.

Perceived stress will be assessed using the short form perceived stress scale.^61^ There may be a risk that participants experience an increased level of stress as they change their behaviours, for instance, many may have used smoking as a destressor. Findings in relation to this outcome may be useful to address such hypotheses in future research.

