### Models

#### Objective 1: primary and secondary outcomes

Analyses of primary outcomes will be conducted among those fulfilling the respective criteria for inclusion at baseline, for example, weekly alcohol consumption will be analysed among those who reported having consumed 10/15 (female/male) or more units of alcohol the past week. BMI, candy/snacks and stress will be analysed among all participants, and number of cigarettes smoked weekly among baseline smokers.

Weekly alcohol consumption, frequency of heavy episodic drinking per month, weekly intake of candy and snacks, number of sugary drinks per week, and cigarettes smoked per week are all count variables that are likely skewed and over dispersed. Therefore, these outcomes will be analysed using negative binomial regression. If found not to be over dispersed, we will consider using normal regression (possibly log-transformed). Average intake of fruit and vegetables per day, MVPA minutes per week, BMI, and stress will be analysed using normal regression (possibly log-transformed). Point prevalence of smoking abstinence will be analysed using logistic regression.

All models will be adjusted for age, gender and mediators at baseline. We will investigate pairwise interactions among components. Effect modification will be explored in all models to assess if any of the baseline characteristics moderate the effects of the components of the intervention.

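### Heavy episodic drinking includes occasions of exactly 4/5 drinks for eligibility and the analysis set but excludes them from the primary outcome, so some analysed participants start at zero

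*Protocol article*

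**What the plan says.** Three places in the protocol article together define who is analysed for heavy episodic drinking and what is counted.

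- **Study setting, recruitment and eligibility.** A student qualifies on this behaviour by having "consumed 4/5 (female/male) or more standard drinks of alcohol on a single occasion at least once the past month". The answer comes from the baseline questionnaire, "which will also be used to assess eligibility for the trial".
- **Objective 1: primary and secondary outcomes.** "Analyses of primary outcomes will be conducted among those fulfilling the respective criteria for inclusion at baseline". The eligibility rule is therefore also the rule for the analysis set. The episode count is one of the count variables for which the plan states that "these outcomes will be analysed using negative binomial regression".
- **Primary and secondary outcome measures.** The outcome itself is "how many times they have consumed more than 4/5 (female/male) standard drinks of alcohol on one occasion the past month".

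The outcome is primary: the list under Primary outcome measures gives, for alcohol, "weekly alcohol consumption; monthly frequency of heavy episodic drinking". Under Sample size, effect, harm and futility, every component is checked against effect, harm and futility criteria for each primary outcome, with an interim analysis for every 50 participants who complete the 4-month follow-up.

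**The concern.** Eligibility and analysis set include an occasion of exactly 4 drinks (women) or 5 drinks (men). The outcome excludes it. The cut therefore falls on the lowest number of drinks that brings a student into the analysis for this outcome.

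Two things are at stake. The first is meaning: the outcome does not count all of the behaviour that the trial treats as risky, so a change in the count is not the same as a change in that behaviour. The second is information: people who enter on occasions of exactly 4/5 drinks add zeros to the count, and their improvement on those occasions cannot be seen.

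Precision matters because the stopping criteria are tight. If the posterior is roughly normal and centred at zero, the futility criterion (more than 95% of the probability within ±0.10) needs a posterior standard deviation of about 0.10/1.96 = 0.051. The effect criterion needs the same value when the posterior median sits at its 0.10 bound.

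**Working it through.** The article gives no figure to reproduce here, so the check sets the definitions side by side and follows individual participants through them. I assume that drinks are reported in whole numbers.

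**Step 1. Thresholds in whole drinks (women / men).**

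| Use | Rule | Smallest occasion that counts |
|---|---|---|
| Eligibility | at or above 4 / 5 | 4 / 5 |
| Analysis set (inherits eligibility) | at or above 4 / 5 | 4 / 5 |
| Primary outcome | strictly above 4 / 5 | 5 / 6 |

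The gap is 5 − 4 = 1 drink for women and 6 − 5 = 1 drink for men.

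**Step 2. Baseline, by largest occasion in the past month.**

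| Largest occasion (women / men) | Analysed for this outcome? | Baseline count under the outcome wording |
|---|---|---|
| 3 / 4 | no | 0 |
| 4 / 5 | yes | 0 |
| 5 / 6 | yes | at least 1 |

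The middle row is the problem: those participants are in the analysis set with no episode on the outcome's own definition.

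**Step 3. Follow-up, by largest occasion in the past month.**

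| Largest occasion (women / men) | Scores an episode? | Still meets the risk criterion? |
|---|---|---|
| 3 / 4 | no | no |
| 4 / 5 | no | yes |
| 5 / 6 | yes | yes |

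**Step 4. Combine the two.**

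- From 4 / 5 down to 3 / 4: the person leaves the risk group, but the count is 0 both times. A real improvement is not recorded.
- From 5 / 6 down to 4 / 5: the count falls to 0, yet the person still meets the risk criterion. The episode is recorded as eliminated.
- From 4 / 5 up to 5 / 6: the count rises from 0 to at least 1. The zero is certain at baseline only.

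**Step 5. What the questionnaire might say.** The items are in online supplemental appendix B, which is not shown. There are three possibilities.

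1. All items use strictly above 4/5. The questionnaire then cannot identify people at exactly 4/5, and the published eligibility rule and analysis set are not what is applied.
2. All items use at or above 4/5. The published description of a primary outcome is then wrong.
3. The baseline and follow-up items differ. Counts are then not comparable over time.

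In each case at least one of the published passages, or an item, needs correcting.

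**Step 6. Size.** The size of the effect depends on the share of the analysis set whose largest baseline occasion is exactly 4/5, and on how many of them stay at or below that level. The article gives neither.

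**The case against.** The strongest reply is that this may be one loose phrase in a condensed article. If a single item with a single threshold serves for both eligibility and outcome, eligibility on this behaviour is simply a count of at least one. No analysed participant then starts at zero, and only the text is wrong. That is possible and cannot be excluded without appendix B. It limits the practical consequence but does not remove the inconsistency, because the published text gives two definitions for a primary outcome.

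It is also fair to say that randomised components are compared on the same follow-up measure. No bias between the levels of any factor is demonstrated.

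Three stronger readings are tempting, and the documents do not support them.

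- *Some participants can never score an episode.* Each follow-up asks about a new past-month window, and nothing stops someone at exactly 4/5 drinks at baseline from exceeding it before 2 or 4 months.
- *The loss of precision can be stated as a percentage of the sample.* Such a figure would treat a share of participants as permanent zeros and would need an assumed share and an assumed dispersion. The article supplies none of these.
- *Baseline and follow-up counts are not comparable.* That requires the items to differ between occasions, and the article does not say that they do.

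**Conclusion.** The inconsistency stands: eligibility and analysis set use at or above 4/5 drinks, the primary outcome uses strictly above 4/5, and the article does not reconcile them. Applied as written, the outcome leaves out occasions that made some participants eligible. Those whose largest baseline occasion was exactly at the threshold start at zero and cannot show a reduction, and a one-drink drop across the outcome threshold is scored as success in someone who still meets the risk criterion.

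This may dilute component effects and reduce precision for an outcome that feeds the interim decisions. The size is unknown. The consequences for individual participants rest on whole-drink reporting and on the published wording being what the questionnaires apply. The inconsistency in the text rests on neither. The article does not show which threshold is intended. The matter should be corrected, but it does not by itself invalidate the comparison between factor levels.

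**What to change.** Bring three sections to a single threshold, so that the analysis set and the outcome count the same occasions: Study setting, recruitment and eligibility; Primary and secondary outcome measures; and Objective 1: primary and secondary outcomes. The trial team must say which threshold was meant. Either closes the gap if it is used throughout, because everyone in the analysis set then has at least one qualifying episode at baseline.

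Then confirm that the baseline item, the 2-month and 4-month items in appendix B and the script for the follow-up telephone calls all use that wording. The calls matter because they collect the primary outcomes from participants who did not respond to the 2-month or 4-month questionnaire.

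The cost is a wording correction. If an item has to change after recruitment has begun, add a note with the date of the change, so that responses before and after can be told apart.

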### Participant timeline and follow-ups

A trial participant timeline is presented in figure 1. Intervention components (depending on allocation) will be made available to participants all at once and stay available to participants at their own discretion throughout the 4-month trial period. There are three follow-up stages: 1, 2 and 4 months after randomisation. All follow-ups will be initiated by sending text messages to participants with hyperlinks to questionnaires. The following additional attempts will be made to collect data:

A total of two text reminders will be sent 2 days apart to those who have not responded.If there is no response to the mediator questions at the 1-month follow-up, then the questions will be sent in a text message and participants are asked to respond directly with a text.If there is no response to the 2-month and 4-month follow-ups, then we will call participants to collect responses for the primary outcome measures only. A maximum of five call attempts will be made.

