## Analysis

Analyses will be done under the intention-to-treat principle including all randomised participants. Analyses will be done using available data and imputation. Imputation will be done using multiple imputations with chained equations.^68^ The implicit missing at random (MAR) assumption underlying this approach will be investigated by two attrition analyses: (1) if data is missing systematically then it may be the case that early responders (ie, those who answer without reminders) differ from non-responders, and in extension that late responders (ie, those who require several attempts) are more alike non-responders. Therefore, one attrition analysis will regress primary outcomes against number of attempts to collect follow-up before a response was recorded; (2) we will further explore the MAR assumption by investigating if responders and non-responders are different with respect to baseline characteristics.

Longitudinal data will be analysed using multilevel models with adaptive intercepts for participants and time by component interactions. Bayesian inference will be used to estimate the parameters of the models^30 31 69^ (see Sample Size for priors). For each condition by time coefficient, we will report the marginal posterior probability of effect, and the median will be used as a point estimate of the magnitude of the effect. We will also report on 50% and 95% compatibility intervals.

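### Telephone follow-up records smoking abstinence but not the weekly cigarette count, so the available-data analysis of that secondary outcome loses smokers and keeps abstainers

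*Protocol article*

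**What the plan says.** Abstinence is a primary outcome and the weekly cigarette count is a secondary one, listed as "Number of cigarettes smoked the past week". Four statements in the protocol article determine what data the count will have.

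- **Who is asked** (Primary and secondary outcome measures): "Participants who have smoked any cigarette the past 4 weeks will be asked for the number of cigarettes smoked the past week".
- **What a call collects** (Participant timeline and follow-ups): if the 2-month and 4-month text messages go unanswered, "then we will call participants to collect responses for the primary outcome measures only".
- **Who is analysed and how** (Objective 1): "number of cigarettes smoked weekly among baseline smokers". For the count outcomes as a group, "these outcomes will be analysed using negative binomial regression", unless they prove not to be overdispersed.
- **Missing data** (Analysis): "Analyses will be done using available data and imputation", with multiple imputation by chained equations under a missing-at-random assumption.

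**The concern.** The intended population is all baseline smokers, but the collection rules do not give every responder in it a count. An online responder has one either way: smokers report it, and abstainers have 0 by logic. A telephone responder has a count only if abstinent.

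Within the telephone group, then, the known values are all zeros and the unknown values all belong to people who smoked. Missingness follows smoking status, which is itself a primary outcome that a component may change. A model fitted to the available counts, with the listed covariates (age, gender, baseline mediators), does not condition on that status. It will understate mean consumption, and understate it more wherever more people have quit. At stake is how far the secondary result can be trusted alongside the primary abstinence result.

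**Working it through.** The protocol states no figure for this outcome, so there is nothing of its own to reproduce. The check is a closed-form calculation on assumed inputs.

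**Inputs**
- From the protocol: the telephone rule, the follow-up filter, and the baseline-smoker population.
- Assumed: abstinence q0 = 20% without the component and q1 = 25% with it; the same mean count m among continuing smokers in both groups; a telephone share p of 20%, 30% or 50% of responders, equal in both groups and unrelated to smoking status; abstainers entered as 0, including those reached by telephone.

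**Formulae**
- True mean = (1 − q) × m.
- Available-data mean = m × (1 − p)(1 − q) / [(1 − p) + p × q]. The denominator counts all online responders plus the telephone abstainers.

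**True ratio:** 0.75 / 0.80 = 0.9375, or 0.94.

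**Available-data results, in units of m**

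| p | Without component | With component | Ratio | Mean without component understated by |
|---|---|---|---|---|
| 20% | 0.64/0.84 = 0.762 | 0.60/0.85 = 0.706 | 0.93 | 1 − 0.762/0.80 = 5% |
| 30% | 0.56/0.76 = 0.737 | 0.525/0.775 = 0.677 | 0.92 | 1 − 0.737/0.80 = 8% |
| 50% | 0.40/0.60 = 0.667 | 0.375/0.625 = 0.600 | 0.90 | 1 − 0.667/0.80 = 17% |

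**Direction.** The observed ratio equals the true ratio times [1 − p(1 − q0)] / [1 − p(1 − q1)]. When q1 exceeds q0 this factor is below 1, so benefit is exaggerated. When q1 = q0 it is 1, so with equal telephone shares no effect is created from nothing.

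**Second set of assumptions.** Take half light smokers (10 per week) and half heavy smokers (60 per week). Quitting is 20%/10% (light/heavy) without the component and 40%/10% with it. The true means are 31 and 30, a ratio of 0.968. At telephone shares of 20%, 40% and 60% the available-data ratios are 28.235/29.880 = 0.945, 25.714/28.182 = 0.912 and 21.818/25.306 = 0.862. Mechanism and direction are the same.

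**Scale against sampling error.** If the survey's 17% smoking prevalence applied, 2500 participants would include about 425 baseline smokers. In 2000 simulated trials of that size on the second set of assumptions, with complete zero-coded counts, the median ratio was 0.969 and 60.2% of runs fell below 1. That implies a standard error of the log ratio near 0.031/0.26 = 0.12. In the first set, the shifts from 0.9375 are ln(0.84/0.85) = −0.012, ln(0.76/0.775) = −0.020 and ln(0.60/0.625) = −0.041. These are roughly 0.1, 0.2 and 0.3 of a standard error.

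**The case against.** **The calls are short on purpose.** They are a last resort after unanswered reminders, and the authors discuss burden and attrition openly. Every secondary outcome is left off the call, not only this one. That stands as a reason for the general rule. This count differs in that its missingness is tied to an answer recorded on the same call.

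**Imputation already covers it.** Smoking status is recorded on the call. Given that status the count may be missing at random, which chained equations can handle. This is largely right, but only if status enters the imputation model, and the available-data analysis gets no such help. Imputation would also borrow from smokers who answered online, whereas the Analysis section itself raises the possibility that late responders differ. Asking avoids that assumption. In the multilevel model, a count given online at the other time point may recover part of the loss.

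**The zero coding is assumed.** If telephone abstainers were left missing as well, the dependence on status would go. Known zeros would be discarded, however, and the whole late-responding group would drop out of the outcome.

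**A stronger reading is tempting.** A reader might infer from the filter that quitters drop out of the analysis and that a component which helps people quit could appear to raise consumption. The protocol does not support this. The population is baseline smokers, the unasked value is a logical 0, negative binomial regression accepts zeros, and the coding of a questionnaire skip is normally left to the analysis plan. Even if quitters were dropped, reversal would need extra quitting concentrated in light smokers. On the second set of assumptions that case gives 1.10 against a true 0.97. Equal quitting rising from 20% to 30% in both strata gives 1.00 against 0.875. Extra quitting mainly in heavy smokers (25%/20%) gives 0.98 against 0.90.

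**Conclusion.** The point holds for the telephone rule. The protocol itself fixes what a call collects, and a later analysis plan cannot recover a count that was never asked. With abstainers at 0, the available-data contrast is modestly biased in the direction of the abstinence effect: a true 0.94 becomes 0.93 to 0.90 for telephone shares of 20% to 50%, and the mean without the component is 5% to 17% too low.

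The quit rates, telephone shares and equal consumption among smokers are all assumptions. The direction also needs similar telephone shares in the two groups. With no effect (abstinence 20% in both) but shares of 20% without and 30% with the component, the ratio would be 0.737/0.762 = 0.97; with the shares swapped it would be 1.03.

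The consequence is limited. The outcome is secondary, the stopping criteria use primary outcomes only, and abstinence itself is collected by telephone. The change is worth making because it is cheap. No claim of sign reversal is made.

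**What to change.** 1. In Participant timeline and follow-ups, add the past-week cigarette count to the telephone script for baseline smokers who report having smoked.
2. State that a baseline smoker who reports abstinence over the four-week filter is entered as 0, whether online or by telephone, before modelling and imputation.
3. Impute any count still missing conditional on reported smoking status, and use that analysis for this outcome in place of the available-data one.
4. Reconcile the two time windows in the abstinence definition: "Four-week point prevalence of smoking abstinence (no cigarettes the past week) will be asked as a binary question". Abstinence under either window implies a past-week count of 0. Under a four-week window, however, some who report smoking will have had none in the past week, so imputed counts must be allowed to be 0.

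The cost is one question and a few seconds on some calls, plus a one-line derivation rule.
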